#### 2.2.2 The SOUND intervention

The intervention will be implemented in Italy, in an Alzheimer day-care center, and in Portugal and Romania, in older people care facilities hosting people with dementia, where the DCPs who will be involved would regularly work. It includes 12 sessions delivered twice a week, for a 6-week period. Although there is no consensus regarding the frequency required for music-based interventions (Moreno-Morales et al., 2020), past research suggests that a higher occurrence may be more impactful (Carr et al., 2013).

During the intervention, OPDs and DCPs are positioned in a circle and everyone plays a specific role within the circle. OPDs will be the participants to whom the intervention is delivered. DCPs will implement the intervention by undertaking specific roles, i.e., the roles of facilitator, co-facilitator or internal observer. The role of facilitator will be assigned to a musician or a DCP with music skills, previously trained in the SOUND method. During the sessions, the facilitator proposes the activities to the participants in a responsorial style, holds the circle, welcomes and repeats any spontaneous and unexpected activity coming from the participants and proposes it to the whole circle. A DCP will be the co-facilitator, who is responsible for supporting the facilitator during the session. The role of internal observers, generally four per SOUND session, will be assigned to the rest of recruited DCPs: their task is to support the OPDs during the intervention in a non-intrusive and facilitating way while taking part in the activity. Facilitator, co-facilitator and internal observers take mental notes of their observations for reporting them in writing at the end of each session by using the live monitoring tools reported in Table 2. Four researchers (for covering all the sections of the circle circumference) will be the external observers: they will focus on OPDs’ emotional and behavioral responses to the proposed activities and take notes through dedicated tools (Table 2).

**TABLE 2 T2:** Live monitoring outcomes tools.

Target group	Tools	Variable	Point of view	When it is used
Dementia care professionals	Video recording	Behavior	Video camera (researcher)	During SOUND sessions
	Live Session Emotions Thermometer	Emotional state, behavioral reaction	Self-report	After each SOUND session
Older people with dementia	Video recording	Behavior	Video camera	During SOUND sessions
	Live Session Emotions Thermometer	Emotional state, behavioral reaction	Internal observer	During SOUND session
	AARS	Affect	External observer	During SOUND sessions

Each SOUND session lasts about 45 min and it is divided in four different phases: (1) welcoming; (2) opening activity; (3) three to five main activities depending on the length and intensity of each one; (4) closing activity. To every phase, except for phase 3, an exercise corresponds.

The intervention foresees both active (vocal and rhythmic production) and passive (listening to pieces of music) music-based activities. Additionally, narrative activities may be linked to the music, such as creating or telling stories, talking about pictures, describing an object and so on. All activities have the general objective of enhancing participants’ wellbeing. Additionally, each activity aims to stimulate specific cognitive abilities. The goal is not to complete an exercise correctly, on the opposite the facilitator has the task to adapt activities to the group participants and use what is generally considered as a mistake as a resource to creatively change the activity. Therefore, the focus is on inclusion rather than on performance.

All the activities are chosen based on: (a) OPDs’ personal music preferences identified by means of a biographical sheet, as detailed below; (b) OPDs’ level of impairment; (c) the objective of the stimulation activities e.g., verbal fluency, memory, coordination. Activities are also organized taking into account particular fears and triggering factors of OPDs based on their personal stories and current situations, checked through the biographical sheet.

The activities proposed are personalized based on the OPDs’ preferences and on their actual mental and physical condition, thus they may need to be adapted from time to time and from person to person. For an example of activities, see Annex 1.

#### 2.2.3 The environment

The literature shows that there is a connection between certain characteristics of the environment and OPDs’ physical functioning, emotional well-being and social interaction (Calkins, 1988, 2001; Day and Calkins, 2002; Marcus, 2007; Marquardt and Schmieg, 2009; Chaudhury and Cooke, 2014). Chaudhury et al. (2016) underlines the need for creating physical environments appropriate and responsive to cognitive abilities and functioning of OPDs living in residential facilities and day care centers.

It is well-known that since neurological disorders can alter OPDs’ senses, i.e., their perception of reality, especially the sight, well-designed environments can promote wayfinding and orientation (Marquardt and Schmieg, 2009), improve activities of daily living function (Reimer et al., 2004), autonomy and meaningful activity (Kane et al., 2007), and reduce anxiety, agitation, aggression (Schwarz et al., 2004).

Homelike environments (i.e., open-plan lounge/dining areas, residential furniture and flooring) displayed reduced verbal and overall aggression, verbal agitation and anxiety (Zeisel et al., 2003; Wilkes et al., 2005), are associated with fewer walking/pacing episodes, (Yao and Algase, 2006) and enhance engagement in daily activities, social interaction (Campo and Chaudhury, 2011) and autonomy (Chaudhury et al., 2016).

High noise levels, such as for example alarms, rings and staff conversations not including older users, are associated with the latter’s reduced social interaction, increased agitation and aggression, disruptive behavior and wandering (Campo and Chaudhury, 2011; Garcia et al., 2012; Garre-Olmo et al., 2012; Joosse, 2012).

The intensity of the light is also important for creating a welcoming environment for OPDs. In fact, the exposure to a bright light can decrease agitation and disruptive behavior and improve cognition and mood, albeit modestly (Nowak and Davis, 2010).

This is the reason why it is very important that the room hosting the SOUND activities is homelike displayed, welcoming, with soft light and that the level of noise is very low, for favoring concentration and cognition. The room will need to be large enough to allow participants movement, tidy with as little distracting objects as possible, with a suitable level of light which is not too dark and not too bright, and with small sound reverberation. The chairs need to be arranged in a circle with assigned seats (placing a sheet on each chair, where the name of each participant is written) taking into account specific aspects for interacting with the OPDs: (a) interpersonal dynamics; (b) visual/auditory difficulties; (c) need for proximity to the healthcare staff; (d) definition of roles. Considering the space of the circle as inside a square, one chair for each corner needs to be positioned outside the circle for the external observers.

### 2.3 Outcome measures and data collection tools

#### 2.3.1 Outcome measures

The primary outcome variable for OPDs is the level of their mental wellbeing, while the primary outcome variable for care professionals is the level of burnout. Secondary outcomes variables for DCPs are (a) level of stress, (b) level of work cooperation and of (c) emotional well-being and, for OPDs, they are levels of (a) cognitive abilities, (b) neuropsychiatric symptoms, (c) mood and (d) emotional well-being.

Pre, post and longitudinal-intervention outcome (Table 3) as well as live monitoring tools (Table 2) were developed for assessing the impact of the SOUND intervention on DCPs and OPDs.

**TABLE 3 T3:** Pre, post and longitudinal-intervention outcome tools.

Target group	Tools	Variables	Who administers the tool	Who answers the questions	When it is used
DCPs	Burnout Assessment Tool (BAT)	Stress	Care professional	Care Professional	T0, T1, T2
	*Ad hoc* questionnaire	Stress	Care professional	Care professional	T0, T1, T2
	*Ad hoc* questionnaire	Work cooperation	Care professional	Care professional	T0, T1, T2
	Longitudinal Emotional Well-being thermometer (LEWT)	Emotional wellbeing	Care professional	Care professional	Daily report from T0 to T2
OPDs	Neuropsychiatric Inventory (NPI)	Neuropsychiatric symptoms (patient) and Caregiver Distress	Psychologist	Family caregiver	T0, T1, T2
	MoCA	General cognition	Psychologist	Older person	T0, T1, T2
	FAB	Cognition – Executive functions	Psychologist	Older person	T0, T1, T2
	HADS	Mood	Psychologist	Older person	T0, T1, T2
	WHO (Five) Well-Being Index (WHO-5)	Wellbeing	Psychologist	Older person	T0, T1, T2
	Longitudinal Emotional Well-being Thermometer (LEWT)	Emotional wellbeing (of patient)	Family caregiver	Family caregiver	Daily report from T0 to T2

#### 2.3.2 Pre-post and longitudinal tools

Concerning DCPs, an *ad hoc* questionnaire has been developed to investigate the level of stress and cooperation of professionals before and after the intervention. Beyond the demographic questions (i.e., age, gender, nationality, marital status, education), the pre-intervention questionnaire includes *ad hoc* questions on: (a) work condition (e.g., position, role, activities); (b) music attitudes; (c) well-being, motivation, satisfaction and self-realization at work (d) teamwork, (e) relationship with patients and family caregivers. Additionally, the Burnout Assessment Tool (BAT) will be administered for evaluating the work-related stress. Respondents can answer all the questions (i.e., both *ad hoc* questions and the BAT battery) through a five-point Likert scale, where 1 represents the lower and 5 the higher score/frequency. The post-intervention questionnaire for DCPs follows the same structure of the pre-intervention ones, except for quantitative and qualitative questions asking to what extent and how the intervention has improved every area e.g., well-being, team work, relationship with OPDs.

The Burnout Assessment Tool (BAT) is a self-assessment questionnaire that measures parameters associated with burnout (De Beer et al., 2020; Schaufeli et al., 2020) validated in Italy (Angelini et al., 2021; Borrelli et al., 2022), in Romania (Oprea et al., 2021), in Portugal (Sinval et al., 2022) and with European cut-off scores (Schaufeli et al., 2023). The BAT contains four different subscales: exhaustion, mental distance, loss of emotional control and loss of cognitive control. In addition, there are two sub-dimensions: psychological disorders and psychosomatic disorders. In total, the questionnaire consists of 33 items (23 for the reduced version), each with a 5-point scale (1 = never, 2 = rarely, 3 = sometimes, 4 = often and 5 = always). The total score is obtained by summing the points. A difference of ± 10 points with a 95% confidence interval shows significance in the variation of burnout (Daniels et al., 2022). The BAT will be the tool to assess the primary outcome for DCPs.

For the OPDs, demographic and baseline data will include age, gender, nationality, marital status, education, living condition, dementia service they attend, type of diagnosis, time of diagnosis, level of verbal expression and comprehension. As outcome tools, the following psychometric and standardized measures will be used.

The Neuropsychiatric Inventory (NPI) is a tool to assess dementia-related behavioral symptoms by examining 12 sub-domains of behavioral issues: delusions, hallucinations, agitation/aggression, dysphoria, anxiety, euphoria, apathy, disinhibition, irritability/lability, aberrant motor activity, night-time behavioral disturbances and appetite and eating abnormalities (Cummings et al., 1994; Cummings, 1997, 2020). The inventory is administered by a health professional to the primary family (if the older person lives in the community) or professional caregivers (if the older person lives in a care home). Each sub-domain includes a screening question followed by a sub-list of questions to answer if the behavior is present, which rate the frequency (4-point scale) and severity (3-point scale) of symptoms plus the level of distress caused to the caregiver (5-point scale). The measure provides a total score for BPSD ranging 0–144 and for caregiver’s stress from 0 to 60. The validity and reliability of the tool is well established even across translations (Farina et al., 2009; Ferreira et al., 2015).

The Montreal Cognitive Assessment (MoCA) is a brief screening tool for detecting mild cognitive impairment and dementia, which is divided in seven domains and sub-scores: orientation (6 points); attention (6 points); memory (5 points for delayed recall); visuospatial/executive (5 points); naming (3 points); language (3 points); abstraction (2 points); if the person has ≤ 12 years of education a further point will be added (Nasreddine et al., 2005). The test has been shown to have good validity, internal consistency, test–retest and inter-observer reliability (e.g., Freitas et al., 2013) and it is used worldwide.

The Frontal Assessment Battery (FAB) is a short neuropsychological tool aiming to assess executive functions or functions related to the frontal lobes and correlated with frontal metabolism (Sarazin et al., 1998). It includes 6 subtests one for each investigated cognitive function: similarities test (conceptualization and abstract reasoning); verbal fluency test (mental flexibility); Luria motor sequences (motor programming and executive control of action); conflicting instructions (sensitivity to interference); go–no go test (inhibitory control); prehension behavior (environmental autonomy). The scoring for each subtest is from 0 to 3, for a maximum total score of 18 (highest performance). The battery has good validity (correlation of ρ = 0.82 with the Mattis Dementia Rating Scale) and interrater reliability (κ = 0.87) (Dubois et al., 2000).

The Hospital Anxiety and Depression Scale (HADS) is a 14-item self-report measure for screening anxiety (7 questions) and depression (7 questions) states. The Likert-scale ranges from 0–3 for a maximum total score of 21, with higher scores indicating greater anxiety and depression, and with a cut-off > 10 (Zigmond and Snaith, 1983). It has shown high concurrent validity with other widespread anxiety and depression assessments and has proved a 20-day test-retest reliability of0.94 (Michopoulos et al., 2008). It is widely used in the field of dementia as it is brief, measures both anxiety and depression and is suitable for people with physical comorbidities (e.g., Clare et al., 2012).

The WHO Wellbeing Index (WHO-5) is a self-assessment tool to measure the subjective mental well-being of individuals which is validated for older people (Heun et al., 1999). It includes five items each scored from 0 to 5. The total score ranges from 0 to 25, with higher scores indicating greater mental well-being. Scores < 13 indicate poor well-being and suggest depression according to the criteria of the International Statistical Classification (Tiganov et al., 1997). It is recommended to transform the raw scores to percentage scores, by multiplying it by 4, for data analysis when investigating change over time (Topp et al., 2015). Low mood may be suggested by a percentage score of ≤ 50 whilst a score of ≤ 28 may indicates depression. Similar to Kikuchi et al. (2023), a variation of ± 10 points of the percentage score with 95% confidence intervals will be considered significant. The reliability and validity of the WHO-5 is well established (e.g., Bech, 2012; Takai et al., 2013). The WHO-5 will be the tool to assess the primary outcome for OPDs.

The SOUND consortium developed the Longitudinal Emotional Well-being Thermometer (LEWT), an idiosyncratic tool for monitoring the emotional well-being of DCPs and OPDs from T0 to T2 on a daily basis for the overall duration of the intervention. This is a self-report tool for the professionals and an observation-based tool for primary family or professional caregivers to record OPDs’ emotional state. Both versions include the picture of a colored thermometer, with each color indicating an emotional range and corresponding to a score. The color and the scoring have been assigned on the basis of the quality and level of neurophysiological arousal (i.e., parasympathetic and sympathetic systems): green indicates a homeostatic state of peace and calm (score = 0); darker green is joy/satisfaction whilst yellow indicates confidence/hope (score = 1); light blue means worried/anxious versus orange is annoyed/frustrated (score = 2); dark blue indicates sad/depressed whilst red means angry/disgusted (score = 3). The higher the score the greater the emotional distress. DCPs will be asked to rate their prevalent emotional wellbeing state every day, at the end of the day, for 63 days. Likewise, primary family or professional caregivers, who have a pre-existing relationship with the OPD and are able to observe them daily, will be asked to report their cared for mood. The following mean range can be obtained from the total sum divided by the total days: scores from 0 to 1 indicate well-being, scores from 1 to 2 indicate mild emotional discomfort, and scores from 2 to 3 indicate emotional distress. Each emotional state will also have a code 1–7 to identify the type of emotion and calculate its prevalence throughout the intervention. Additionally, both versions include a final column in order to: (a) rate (on a 1–5 scale ranging from “not at all” to “completely”) how much the recorded emotion may be linked to SOUND sessions for health professionals; (b) record meaningful events in the daily life of OPDs which may be related to their emotional state. The results from the scoring can be summarized in a graph showing the daily trend of the emotional arousal, the frequency of each emotional group and their relationship to the SOUND intervention. The minimum detectable change and the threshold of clinical improvement will be calculated.

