Concerning the impact of the intervention on DCPs, we expect that: (a) the BAT scores will decrease by ± 10 points with a 95% confidence interval; (b) well-being at work, teamwork cooperation and communication with the OPDs will improve of one point on the five-point Likert scale for at least half of the items in each area. For example, to the question “How do you rate the quality of your relationship with older people with dementia?” we expect a minimal change from “Fair” to “Quite good”; (c) the LEWT scores will show a trend toward 0.

It is methodologically worth mentioning that this protocol was designed for DCPs daily working in a dementia care facility. However, the methodology may be applied even by external professionals who have an external collaboration with service providers. In this case, the impact of the caregiver stress, that may be influenced by working in a new workplace, could be measured by adding a question such as “In what way the delivery of the SOUND method in an unusual workplace have influenced your levels of work-related stress?”

One strength of the protocol lies in the use of both quantitative and qualitative data collection tools, and in a multi-method approach that will allow to gather written and visual data that will generate numerical, textual and narrative results. Another strength is the cross-national nature of the study that can provide interesting culture-based tips, since every team will use popular and traditional songs belonging to their context.

One limitation of the study may concern the small sample size at national level that will not allow a generalization of the results. Moreover, the protocol does not foresee the monitoring of clinical parameters such as cortisol, blood pressure as recommended by Uğur et al. (2016). In fact, although it would have been interesting to check the impact of the intervention on these realms, the study did not receive enough funding to cover the expenses for a biochemical investigation.

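### The added post-intervention questions for care professionals ask only about improvement, so they cannot record a worsening attributed to SOUND

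*Protocol article*

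**What the plan says.** Section 2.3.2 introduces the tool as follows: "an *ad hoc* questionnaire has been developed to investigate the level of stress and cooperation of professionals before and after the intervention". Every question, whether ad hoc or from the BAT, is answered "through a five-point Likert scale, where 1 represents the lower and 5 the higher score/frequency". On the later administrations it says: "The post-intervention questionnaire for DCPs follows the same structure of the pre-intervention ones, except for quantitative and qualitative questions", and it describes those questions as "asking to what extent and how the intervention has improved every area e.g., well-being, team work, relationship with OPDs".

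Table 3 schedules the ad hoc questionnaire, for stress and for work cooperation, at T0, T1 and T2. Section 2.4 plans paired comparisons between those time points. The Discussion expects that the work well-being, teamwork and communication items "will improve of one point on the five-point Likert scale for at least half of the items in each area". Its example is a plain level question, "How do you rate the quality of your relationship with older people with dementia", expected to rise by one category.

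The BAT, not the ad hoc questionnaire, is the primary outcome tool for the professionals.

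**The concern.** The added items presuppose benefit. On a scale from less to more improvement there is no value for deterioration, so a professional who thinks SOUND harmed teamwork can at best choose the bottom category, the same answer as a colleague who noticed nothing. The open part of the question carries the same presumption and feeds the thematic analysis.

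This matters because the impact of SOUND on the professionals is one of the two principal aims in the Introduction. The respondents also deliver the intervention themselves, and the article describes no comparison group of professionals. The repeated level items can show that an area declined, but not whether the professional puts the decline down to SOUND. In this questionnaire the added items are the ones that ask about attribution, and they do so in the favourable direction only.

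**Working it through.** The plan gives no figure for these items, so there is none to reproduce. The check has three parts.

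**1. What each type of item can record**

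- *Repeated level item, scored 1 to 5 (Table 3; Discussion example).* From baseline b, the later-minus-baseline change can run from 1 − b to 5 − b:
  - b = 1: 0 to +4
  - b = 2: −1 to +3
  - b = 3: −2 to +2
  - b = 4: −3 to +1
  - b = 5: −4 to 0

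  Worsening can be recorded from any baseline above 1.
- *Added improvement item (section 2.3.2).* It is asked only after the intervention, and its scale measures the amount of improvement. If the lowest category means no improvement, all worsening is recorded as that category. The article does not give the anchors, so this meaning is an assumption.

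**2. Effect on the mean when responses are mixed**

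Assumed, not taken from the article: a share p is one step worse, the same share p is one step better, and the rest are unchanged.

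- Two-sided answer: mean = p × (−1) + (1 − 2p) × 0 + p × (+1) = 0 for every p.
- Improvement-only answer: mean above floor = (1 − p) × 0 + p × 1 = p.

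| p | Two-sided mean | Improvement-only mean above floor |
|---|---|---|
| 20% | 0 | 0.2 |
| 30% | −0.3 + 0 + 0.3 = 0 | 0.7 × 0 + 0.3 × 1 = 0.3 |
| 40% | 0 | 0.4 |

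At p = 30%, the floor category holds 30% + 40% = 70% of respondents. Of these, 30/70 = 43% became worse and cannot be told apart from the unchanged. With the planned 45 professionals, 20% to 40% worse would be 45 × 0.20 = 9 to 45 × 0.40 = 18 people.

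As a second illustration, let perceived change X be normal with mean 0 and an assumed standard deviation SD. The floored mean is E[max(0, X)] = SD/√(2π), with √(2π) = 2.507:

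- SD 0.5: 0.5/2.507 = 0.20
- SD 1.0: 1.0/2.507 = 0.40
- SD 1.5: 1.5/2.507 = 0.60

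**3. When no respondent changes**

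If everyone is unchanged and the lowest category means no improvement, everyone scores the floor and the mean above floor is 0. The shift in part 2 needs some respondents who are better and some who are worse.

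**The case against.** The strongest reply is that the questionnaire does not consist of these items alone. It keeps the structure of the baseline form, is given at all three time points, and is compared within person. The phrase 'except for' could be read as the improvement questions replacing the level items, but the Discussion's example of a one-category rise needs the level item both before and after. So a reader might infer that the questionnaire cannot register deterioration; the article does not support that.

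Nor is there no way to see harm to staff. The BAT can rise. The LEWT scores negative emotions daily and asks professionals how far the recorded emotion is linked to the sessions, which is neutral in direction. The session thermometer (LSET) records professionals' own emotions and reactions after each session. All of this stands. What it leaves open is that the LEWT link covers daily emotion only, not teamwork or relationships.

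A reader might also infer that a null effect must look positive, or that the results for professionals as a whole are biased upwards. Neither follows. A uniform null sits at the floor if the floor means no improvement. The expected results in the Discussion are stated as BAT change, a one-point gain on the Likert items and a LEWT trend, and no success criterion is tied to the improvement questions.

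Finally, the article paraphrases the items in one clause and shows neither stems nor anchors, and an open answer can still volunteer harm. That is a fair limit on certainty, so the point is made about the items as described.

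**Conclusion.** The point holds in a limited form. As described in section 2.3.2, the added questions allow SOUND to be credited with improvement in an area but not blamed for worsening, and their mean tilts towards benefit when responses are mixed. The size is illustrative: 0.2 to 0.4 steps for 20% to 40% moving one step each way, or 0.20 to 0.60 under a normal model with SD 0.5 to 1.5, in each case against a true average of zero. These figures rest on assumed distributions and on the lowest category meaning no improvement.

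The primary outcome, the repeated level items and the LEWT are untouched. This is a flaw in supplementary attribution items, worth correcting because it bears on a principal aim and the instrument may carry over to the full-scale study.

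**What to change.** Reword the added items to: 'To what extent and how has this area changed since the start of SOUND?' Offer five answers: much worse, worse, unchanged, better, much better. If explicit attribution is wanted, the stem can ask how far the intervention has changed the area, provided it stays neutral in direction. Use the same neutral stem for the open question. Report the full distribution for each area, including the share worse, and not only a mean.

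The cost is a small revision of a form first used at T1. Section 2.5 requires a formal amendment, approved by the ethics committees, for changes that may affect study conduct, including study procedures, so one may be needed. According to the Introduction, the intervention was still being planned at the time of writing. If the existing form has already been used, the lowest category can at least be reported as no improvement or worse, with the distribution shown and no mean interpreted as a net effect.
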